## Sample size

Based on data from the REACT feasibility study and historical control data, we conservatively assume that the SD of the primary endpoint is 22%. A sample size of 200 participants will enable a treatment effect of a 10% increase in the mean value of the primary endpoint to be detected with 90% power using a two-sided 5% significance test in the primary analysis. Based on a consensus of expert opinion a difference of 10% is believed to be of minimal clinical relevance. It is expected that a small number of patients will be withdrawn from the study. Reasons for these withdrawals include transfer to participant’s local NICU, withdrawal of parental consent or death.

## Recruitment plan

All babies will be recruited within 24 hours of birth at one of the NICUs that has been approved for study participation. Due to the short time frame from birth to recruitment potentially eligible babies will be identified in a number of ways: (1) liaison with the obstetric team to highlight mothers at risk of preterm delivery, (2) liaison with the neonatal transport team to identify babies who have been born in local units being transferred to a study centre and (3) liaison with the NICU clinical team of study centres. Screening of eligible patients will be undertaken in collaboration with the clinical team and families approached only if considered eligible and the families consent to being approached about study involvement. Screening logs will be reviewed regularly by the coordinating centre to identify any issues around recruitment.

The REACT recruitment centres are level 3 NICUs. They have been selected either because of their previous experience of using CGM in the preterm infant, or they are centres with a proportionately large number of babies which would fulfil the study inclusion criteria and represent an international range of clinical practice and thus provide generalisability of the intervention. The first patient was recruited in July 2016, and the end of study is planned for November 2018.

## Randomisation

Randomisation will take place within 24 hours of delivery and babies will be randomised in a 1:1 ratio into control and intervention arms of the study using a central web randomisation system, TENALEA. The randomisation will use blocked stratified randomisation. The stratification factors will be to recruiting centres and gestation (<26 weeks gestation, ≥26 weeks gestation). The programme will notify the local research team of treatment allocation who will then inform their clinical team regarding the practicalities of management. This is an open study in which the clinical and research teams and parents will be aware of the study arm and intervention.

## Data management and analyses

Data collection will be undertaken from birth to 36 weeks corrected gestational age. If a baby has been discharged from their recruiting NICU, the research team will use local and national databases, local contacts and links with parents to ensure complete follow-up data is obtained. All data will be sent to the coordinating centre in Cambridge where it will be entered onto a MACRO database. All data will be collected, transferred and stored to comply with Good Clinical Practice (GCP) and Data Protection legislation. Access to data will only be granted to authorised personnel involved in study management or for auditing/monitoring to comply with regulations. To maintain high-quality standard of data entry, the data base will be tested and validated prior to use.

### Efficacy

This will be assessed by comparison of data collected by real-time CGM in the intervention arm and blinded CGM in the control infants.

### Clinical acceptability

Parents, nurses and medical staff, caring for babies in the study will be asked to complete study-specific questionnaires.

### Safety

This will be assessed in three areas: incidence of hypoglycaemia measured as part of clinical care (BG levels) and after review of SG data; device safety through adverse device effect (ADE) reporting; and acute mortality and morbidity outcomes as part of the case report form (CRF).

### Costs for economic evaluation

Data will be collected on the health service resources used in the treatment of infants during the period between randomisation and 36 weeks gestation and based on British Association of Perinatal Medicine standard criteria for level of care, as well as neonatal complications. Current UK unit costs will be applied to each resource item and a per diem cost for each level of neonatal care will be based on Department of Health reference costs calculated on a full absorption costing basis.

## Data analyses

The primary endpoint will be analysed using linear regression to estimate the absolute difference in time SG in target of 2.6–10 mmol/L, adjusting for baseline variables (centre, gestation). Analyses will be undertaken both for intention to treat and as treated populations. Estimates of treatment effect, with 95% CIs and p values will be provided. Secondary endpoints that are continuous variables will be analysed in a similar fashion. Secondary endpoints that are counts or binary variables will be analysed using an appropriate regression framework. Methods will be used to reduce the likelihood of a type I error. All of the efficacy endpoints will be ranked in order of importance: mean SG, percentage of time SG in target of 4–8 mmol/L, SG variability within individuals as assessed by within-patient SD, percentage of time glucose levels in hyperglycaemic range—SG >15 mmol/L.

Continuous variables will report the mean, median, SD, range, maximum and minimum. Binary or categorical endpoints will be represented using frequency tables in the ‘p% (r/n)’ format. The analysis will look for a treatment interaction effect with the following baseline variables: centre, sex, corrected gestational age, birthweight SDs, use of antenatal steroids, maternal chorioamnionitis and maternal diabetes using the regression framework in an exploratory, non-confirmatory manner.

An incremental cost-effectiveness analysis will be performed. In the baseline analysis, the economic evaluation will be expressed as the incremental cost per additional case of adequate glucose control. Adequate control will be considered as 80% of time in target. Given the multinational nature of the trial, the hierarchical structures of the cost and outcomes data will be taken into account in the analysis plan. Due to the known limitations of within-trial economic evaluations, we will also construct a decision-analytical model to model the cost-effectiveness of CGM beyond the time horizon of the trial.

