## Outcomes

The primary outcome is percentage of time SG in target range of 2.6–10 mmol/L. This was selected after consultation as it represents internationally, the clinically most widely accepted target range for glucose control for this population.

Secondary outcomes have been selected to provide further evidence around efficacy, acceptability and safety. These include for efficacy:Mean SG.Percentage of time SG in range of 4–8 mmol/L.SG variability within individuals as assessed by within patient SD.Percentage of time glucose levels in hyperglycaemic range, SG >15 mmol/L.

Acceptability will be assessed by a specifically designed staff questionnaire which will be completed anonymously on day 3 and 7 by the clinical team caring for the baby as well as a parent questionnaire on day 7.

Safety outcomes include both measures of BG and SG to address potential differences in methodologies and to provide data on prevalence of exposures that may be undetected clinically in the control arm of the study:Incidence of hypoglycaemia defined as any episode of BG >2.2 mmol/L and <2.6 mmol/L.Incidence of hypoglycaemia defined as continuous episode of CGM SG <2.6 mmol/L for >1 hour.Incidence of severe hypoglycaemia defined as any episode of BG ≤2.2 mmol/L.

Health economics: cost-effectiveness will be expressed in terms of incremental cost per additional case of adequate glucose control between 2.6 and 10 mmol/L.

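### The primary model adjusts only for centre and gestation; prespecifying continuous gestational age and birthweight SD score as well would be a cheap efficiency gain of unknown, probably modest size

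*Protocol article*

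**What the plan says.** All references are to the protocol article.

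- **Outcomes:** "The primary outcome is percentage of time SG in target range of 2.6–10 mmol/L", a continuous endpoint.
- **Data analyses:** the primary endpoint is analysed by linear regression, "adjusting for baseline variables (centre, gestation"). Continuous secondary endpoints follow the same approach. The same section lists "centre, sex, corrected gestational age, birthweight SDs, use of antenatal steroids, maternal chorioamnionitis and maternal diabetes" as baseline variables, but only for exploratory treatment-interaction tests.
- **Randomisation:** allocation is stratified by recruiting centre and "gestation (<26 weeks gestation, ≥26 weeks gestation"). The adjustment set therefore consists of the stratification factors. Data analyses does not say whether gestation enters the model as this two-level stratum or as a continuous variable.
- **Sample size:** "we conservatively assume that the SD of the primary endpoint is 22" per cent. The target is a 10% increase in the mean with 200 infants, at a stated power of 90% and a two-sided 5% level. The paragraph does not mention covariate adjustment. It expects a small number of withdrawals, but states no rate and no inflation.

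**The concern.** In a linear model for a randomised comparison, a baseline covariate fixed in advance leaves the treatment estimate unbiased. If it explains part of the outcome variance, it also reduces the standard error. The trial already records birthweight SD score and several other baseline variables. Gestation is also available more finely than the two-level stratum, since the eligibility limit is set in weeks and days. The primary model as written makes no use of the first, and may make no use of the second.

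What is at stake is the width of the confidence interval and some power. The stated inputs put 200 infants just under 90% power, with no stated allowance for withdrawals, so on those inputs alone any precision available from data already collected would be useful.

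**Working it through.** **Inputs.** Difference 10, read as absolute percentage points because Data analyses estimates an absolute difference. SD 22, two-sided 5%, power 90%, N = 200 (Sample size). 1:1 allocation (Randomisation).

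**Step 1: reproduce the stated sample size.** Per arm, n = 2(1.960 + 1.282)² × 22² / 10² = 2 × 10.51 × 4.84 ≈ 101.7, so 102 per arm and 204 in total. The article states 200, which is close enough to count as reproduced.

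**Step 2: power at N = 200.** The standard error is 22 × √(2/100) = 3.111. Then 10/3.111 = 3.214, and 3.214 − 1.960 = 1.254, which gives 89.5%. The noncentral t distribution gives 89.2%.

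**Step 3: effect of extra covariates.** Let R² be the share of the outcome variance remaining after centre and gestation that the added covariates explain. Take 22 as the SD before they are added. The residual SD is 22√(1 − R²), and the equivalent sample size without the covariates is 200/(1 − R²). The article gives no R², so the rows are assumptions. N = 180 is also an assumption (10% not analysed). Powers are from the noncentral t.

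| Assumed extra R² | Residual SD | Power, N = 200 | Power, N = 180 | 95% CI half-width, N = 200 | Equivalent N |
|---|---|---|---|---|---|
| 0 | 22.00 | 89.2% | 85.8% | 6.10 | 200 |
| 0.05 | 21.44 | 90.7% | 87.5% | 5.94 | 211 |
| 0.10 | 20.87 | 92.1% | 89.2% | 5.79 | 222 |
| 0.20 | 19.68 | 94.7% | 92.4% | 5.45 | 250 |

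The half-width is 1.96 × residual SD × √(2/100). For example, at R² = 0.10 it is 1.96 × 20.87 × 0.1414 = 5.79.

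**Step 4: R² needed for 90% power (normal approximation).** The residual SD must be no more than 10 / (3.242 × √(4/N)). This gives 21.81 at N = 200, so R² = 1 − (21.81/22)² = 0.017. The corresponding values are 0.066 at N = 190 and 0.115 at N = 180.

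**Step 5: cost if the covariates are uninformative.** Even five extra terms move the critical t value only from 1.9720 (198 df) to 1.9723 (193 df). Chance imbalance adds roughly 1/200 = 0.5% to the variance per term, or about 1% for two terms. The ratio in Step 2 becomes 3.214/√1.01 = 3.198, and 3.198 − 1.960 = 1.238 gives 89.2% against 89.5% on the same approximation. That is a loss of about 0.3 percentage points, and break-even is an R² of about 0.01.

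**The case against.** The strongest objection is that nothing here is wrong. Adjusting for the stratification factors is standard, valid and consistent with the design, and a longer covariate list may be no more than a reviewer's preference. That stands, and it is why this point is an efficiency suggestion only.

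Three stronger readings are tempting, and the article supports none of them.

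- **Precision is demonstrably being lost.** The article calls the other variables baseline variables. It does not call them predictors of time in target, and it gives no correlation or R². A planned exploratory interaction test concerns effect modification, which is a different property from prognostic value. Centre and gestation may already capture part of whatever these variables would explain.
- **The trial has no power to spare.** The SD of 22 is described as conservative, and the article does not say whether it is marginal or residual. If it is marginal, adjustment for centre and gestation already brings a gain that Step 2 does not count. As an illustration only, a residual SD of 20 would give about 94% power at N = 200 and 92% at N = 180 with no extra covariates. What can be said is that the stated inputs leave no margin.
- **Gestation is reduced to two categories and its information thrown away.** The coding is not stated and may properly sit in an analysis plan that is not shown.

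A further objection concerns timing. This is an open trial that has been recruiting since July 2016, so changing the primary covariate set needs care. That stands too: the change is sound only if those making it have not seen outcome data by arm, and only if it names the covariates exactly.

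**Conclusion.** The point holds as a low-severity efficiency improvement. The centre-and-gestation model is valid, and the stated sample size reproduces. Adding continuous gestational age and birthweight SD score would raise power from about 89% to about 91%, 92% or 95% at N = 200 if they explained a further 5%, 10% or 20% of the variance. The half-width of the 95% interval would fall from 6.1 to 5.9, 5.8 or 5.5 points. These R² values are assumptions and the true gain may be near zero, in which case the loss is about 0.3 points of power. The case for the change is that the possible loss is very small and no new data are needed. It does not rest on any shown deficiency in the plan.

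**What to change.** Before any comparative data are examined, state in the analysis plan that the primary linear regression includes:

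- centre;
- the gestation stratum (<26 or ≥26 weeks);
- gestational age as a continuous variable, if it is not already entered that way;
- birthweight SD score.

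Add a simple rule for missing baseline values. Keep the centre-and-gestation model as a sensitivity analysis, and use the same covariate set for the continuous secondary endpoints. Because the study is open, record the date of the change and that those who made it had no access to outcome data by arm.

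The cost is a sentence or two of text, one or two degrees of freedom and one extra model run.

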## Site training

Research teams at each site will be required to have up-to-date GCP training and have undertaken training in study procedures including use of the CGM and Nova Biomedical point of care devices. Paper and online resources as well as a call line will be available to support the research teams.

## Monitoring

Data returns will be continually monitored by the central team for completeness and timeliness of all data returned. Compliance with intervention strategy in each study arm will also be reviewed to ensure there is not ‘crossover’ between study arms. A monitoring plan is in place determining frequency and scope of site monitoring based on continuing risk review. Face-to-face monitoring visits will initially be undertaken within the first 6 months and then adjusted following assessment of recruitment rate, number of data queries and serious adverse event (SAE) reports. The study sites will provide direct access to all trial-related source data and reports for the purpose of monitoring and auditing by the central study team, sponsor and regulatory authorities as required.

## Data and safety monitoring

The data and safety monitoring committee (DSMC) is responsible for safeguarding the interests of the trial participants and making recommendations to the trial steering committee (TSC). The REACT DSMC roles and responsibilities and operating procedures are defined in the REACT DSMC Charter. It is composed of three independent multidisciplinary experts who are not involved in the conduct of the trial in any way. They met prior to the initiation of enrolment and determined a plan to review the protocol, compliance, safety and AEs and outcome data after a prespecified number of babies have been recruited. The TSC is composed of five to six independent members and has a Charter defining the member’s roles and responsibilities. The TSC provide advice, through its chair, to the chief investigator and report to trial sponsor and trial funder.

Safety will be assessed continuously during each baby’s stay in NICU. The frequency of AE and SAE as defined by The International Conference on Harmonisation and that would normally require reporting within a clinical trial is anticipated to be high in the population being studied despite the low risk of the study intervention. Following discussions with the Medicines and Healthcare Products Regulatory Agency (MHRA) and in accordance with regulatory guidance which allows for exceptions in such circumstances a modified reporting plan was agreed.

Any ADE will be recorded and reported to the coordinating centre. All device deficiencies that might have led to a serious ADE (SADE) if suitable action had not been taken; intervention had not been made or if circumstances had been less fortunate, will be reported to the Sponsor as for SAEs/SADEs. AEs will be recorded in the notes and some will be captured as exploratory outcomes as part of the CRF. SAEs are common in this population, therefore, the MHRA requested the following expectation for safety reporting:

### During the intervention period of the study (study days 1–7)

The following expected SAEs will need to be recorded in the CRF (safety log) and reported using the safety report form to the sponsor within 24 hours of awareness of the event: (1) death, (2) culture positive infection, (3) severe hypoglycaemia (<2.6 mmol/L), (4) seizures, (5) any other related SAE.

### Postintervention period (study day 7 until end of study)

Important medical outcomes for the trial will be captured in the CRF at the 36 weeks corrected gestation assessment. Other SAEs are anticipated events for this study population and do not need to be recorded or reported separately as an SAE if judged by the clinical team to be unrelated to the study.

## Ethics and dissemination

The investigator or a suitably qualified person designated by the principal investigator will receive written informed consent from the patient’s parent/legally acceptable representative before any trial-specific activity is performed. Clinical trial authorisation has been granted by the MHRA (REF: CI/2016/0011). Written approvals will be received from individual hospital sites prior to recruitment. Approvals have also been obtained from Medical Ethics Review Committee, VU University Medical Centre, Amsterdam and Heath Care Inspectorate (REF: 2017–1 398434/VlO 14949), The Netherlands and the Research Ethics Committee, Sant Joan de Déu Research Foundation, Barcelona, and Ministry of Health Social Services and Equality (REF: 591/16/EC), Spain. The chief investigator will ensure that the trial is conducted in accordance with the principles of the Declaration of Helsinki and in conformity with the medical devices regulations and any relevant amendments. The findings of the trial will be prepared and presented at national and international meetings and conferences and published in peer-reviewed journals by the academic team.

## Patient and public involvement

Consultation with the parents from the local parent support group was undertaken to help inform trial design. Parents are being asked to provide feedback on study involvement as part of the protocol. The TSC includes a lay person. We will send newsletters to parents to update them on study progress.

## Conclusions

The REACT trial is an international multicentre trial which will randomise 200 preterm babies (≤1200 g and ≤24 hours of age) to receive either real-time CGM or standard clinical management of glucose control (with blinded CGM data collection). This study will determine if real-time CGM can support better targeting of glucose control in these babies reducing the risk of both hyperglycaemia and hypoglycaemia. This has the potential to impact on both the acute management, and in the future on outcomes of preterm babies who are at risk from glucose dysregulation.
